### Data analysis

Data will be analyzed according to the intention to treat principle. Data of eligible patients who were randomly offered stereotactic radiotherapy will be compared with eligible patients who were not randomly selected and received standard radiotherapy. In case of dropout (i.e. patients not surviving longer than three months or patients unable to provide pain scores and analgesic use), a worst-case analysis will be performed: dropped-out patients will be classified as non-responders. In case of substantial refusal of the SBRT offer in the intervention arm, instrumental variable analysis will be used to account for non-compliance [26]. The primary outcome (i.e. proportion of patients with response to radiotherapy) will be presented in absolute numbers and proportions. Differences in pain response will be compared by χ2 test. If randomization fails, imbalances between baseline characteristics will be adjusted by logistic regression analysis. Differences in duration of response and overall survival will be analysed by Kaplan-Meier analysis and log rank test. Toxicity will be presented as the overall incidence of grade 3–4 toxicity and incidence of vertebral compression fractures. Differences will be tested with the χ2 test. A comparison in QOL will be made between the baseline QOL and at predefined intervals after treatment. A change of 10% of the scale breadth will be considered a clinically relevant change of QOL [27]. Data will be presented as improved (≥10% increase), stable, or worsened (≥10% decrease) QOL. We will evaluate the pattern of QOL as a continuous outcome over time using mixed models. Differences with a *P*-value <0.05 will be considered statistically significant. We have planned to perform an interim analysis after inclusion of half of the patients (i.e. 55 patients) when they have completed their follow up (i.e. three months pain assessment).

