### Random selection

Eligible patients are randomly selected from the sub cohort on a 1:1 basis with varying block sizes (*n* = six or eight) using an in-house randomization computer program. The radiation oncologist will offer the experimental intervention (i.e. SBRT) to the randomly selected patients. If they accept the treatment offer, they will sign informed consent for participation in the VERTICAL study. Patients who refuse the SBRT will receive care as usual (i.e. standard radiotherapy). According to the cmRCT design, patients in the sub cohort who are not randomly selected will not be informed about the experimental intervention, nor will they be informed about their participation in the control arm of the VERTICAL study. Outcomes in randomly selected patients are compared with the outcomes in eligible patients not randomly selected who received standard radiotherapy (Fig. 1).

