### Sample size considerations

Based on the most recent meta-analysis, we expect a pain response in 60% of patients following standard radiotherapy [3]. Pain response after stereotactic radiotherapy is assumed to be 85% [8, 9]. We expect that approximately 90% of patients who are offered SBRT treatment, will accept the offer. Cross-over from control arm to the SBRT treatment arm is extremely unlikely, since only patients who are randomly selected to receive SBRT are informed about the treatment. Taking a one-sided α of 5% and a power of 80%, we require 49 patients per treatment arm to show a statistically significant difference of 15% in pain response. The reason to choose a one sided α is that, although improbable, inferior pain response after stereotactic treatment would lead to the same action as no difference at all between the two treatment regimen. This is because the SBRT treatment will only be implemented if it is significantly better than the usual care, since SBRT treatment is more complex, less convenient for patients, and more expensive than standard radiotherapy. Finally, to allow for a 10% drop out rate, recruitment of 55 patients per group is intended. We expect to complete recruitment within 18 months based on the number of patients we treat in our center annually.

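### Toxicity and fractures are compared only by offer of SBRT, so refusers given standard radiotherapy dilute any toxicity excess; a table by treatment received should stand beside it

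*Protocol article*

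**What the plan says.** All of this is in the protocol article.

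- **Analysis principle** (Data analysis): "Data will be analyzed according to the intention to treat principle". No outcome is excepted.
- **Groups compared** (Data analysis): "Data of eligible patients who were randomly offered stereotactic radiotherapy will be compared with eligible patients who were not randomly selected and received standard radiotherapy". The contrast is therefore offered versus not selected.
- **Harm outcomes** (Data analysis): "Toxicity will be presented as the overall incidence of grade 3–4 toxicity and incidence of vertebral compression fractures". The differences are tested by chi-squared. No comparison by treatment received is stated.
- **Refusers** (Random selection): "Patients who refuse the SBRT will receive care as usual (i.e. standard radiotherapy").
- **Expected acceptance** (Sample size considerations): "We expect that approximately 90% of patients who are offered SBRT treatment, will accept the offer".
- **Movement the other way** (Sample size considerations): "Cross-over from control arm to the SBRT treatment arm is extremely unlikely".
- **Provision for refusal** (Data analysis): "In case of substantial refusal of the SBRT offer in the intervention arm, instrumental variable analysis will be used to account for non-compliance". The sentence names no outcome and does not define substantial. The Abstract describes this analysis as a complement to intention to treat.
- **Fracture detection** (Secondary endpoints): an additional MRI at six months is scheduled for the SBRT arm. No counterpart is stated for controls.

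**The concern.** In a cohort multiple randomised design, consent to the experimental treatment follows selection, so some refusal in the intervention arm is built in. Because almost no control patient is expected to receive SBRT, the mixing is one-directional: intervention-arm rates move toward control rates and not the reverse.

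For a superiority test of pain response, that movement is conservative. For harm it favours the new treatment, because the excess attributable to SBRT looks smaller than it is among the patients who received it. The sample size section says SBRT would be adopted only if clearly better, given its complexity, inconvenience and cost. The section on SBRT also gives fracture risk as one reason for the integrated boost. A reader weighing benefit against harm will want the toxicity rate in patients actually given SBRT, and the stated analysis does not supply it.

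**Working it through.** **1. The plan's own figure.** The protocol gives no expected rate, power or sample size for toxicity or fractures. The only figure to reproduce is the 49 per arm for pain response. Inputs: 60% response on standard radiotherapy, 85% on SBRT, 90% acceptance, one-sided α of 5%, power 80%.

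Response expected in the offered arm: 0.9 × 0.85 + 0.1 × 0.60 = 0.825.

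With the pooled formula without continuity correction, n = [z_α·√(2p̄(1−p̄)) + z_β·√(p₁(1−p₁) + p₂(1−p₂))]² / (p₂−p₁)², where p₁ = 0.60, p₂ = 0.825 and p̄ = 0.7125:

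n = (1.645 × 0.640 + 0.842 × 0.620)² / 0.225² ≈ 49.

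Then 49 / 0.9 = 54.4, rounded up to 55. So 49 and 55 are reproduced when the efficacy effect is diluted for 10% refusal. (60% versus 85% two-sided also gives 49, but the stated α is one-sided; 60% versus 85% one-sided gives 39.) The sample size therefore appears to allow already for the mixing described here. The difference of 15% printed in that section matches neither 25 nor 22.5 points. That is a separate matter and this point does not depend on it.

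**2. The same mixing applied to harm.** Let a be acceptance, pS the harm rate after SBRT and pC the rate after standard radiotherapy. With no control patient receiving SBRT:

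rate in the offered arm = a·pS + (1−a)·pC

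observed excess = a·(pS − pC) = (1 − refusal) × true excess.

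The relative loss equals the refusal proportion whatever the harm rates are: 10% at the planned acceptance, 30% at 70% acceptance and 50% at 50% acceptance.

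**3. Size in points and power.** The harm rates below are assumptions. Power is two-sided at 5%, pooled, with 55 evaluable patients per arm.

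| Acceptance | 5% vs 15%: excess (power) | 5% vs 20%: excess (power) | 10% vs 30%: excess (power) |
|---|---|---|---|
| 100% | 10.0 (41.5%) | 15.0 (66.6%) | 20.0 (75.3%) |
| 90% (planned) | 9.0 (36.1%) | 13.5 (59.6%) | 18.0 (67.7%) |
| 80% | 8.0 (30.9%) | 12.0 (52.1%) | 16.0 (59.1%) |
| 70% | 7.0 (25.8%) | 10.5 (44.2%) | 14.0 (49.8%) |
| 50% | 5.0 (16.6%) | 7.5 (28.3%) | 10.0 (31.0%) |

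The 100% row assumes all 55 are treated as labelled. A real split by treatment received would be slightly unequal: at 90% acceptance, 0.9 × 110 / 2 = 49.5 on SBRT and 60.5 on standard radiotherapy.

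**4. What an instrumental variable estimate would do.** With one-directional non-compliance, the simple estimate is the intention-to-treat difference divided by acceptance: 13.5 / 0.9 = 15 points in the 5% versus 20% example. It would recover the undiluted excess, but the document does not say whether it would be applied to toxicity.

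**5. Fractures.** Dilution lowers the observed excess. A scheduled MRI in the SBRT arm only raises detection there and pushes the observed excess up. The document gives no figure for either force, so their net effect cannot be signed.

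**The case against.** The case on the other side has five parts.

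*Efficacy is not given a correction that harm is denied.* A reader might infer from the order of sentences that the instrumental variable analysis serves pain response alone: it follows the rule on missing pain data and comes just before the primary outcome. The text does not support that as fact. The sentence names no outcome, and the Abstract words it generally. If the intention-to-treat sentence is read as general, this one can be too. What stands is narrower: nothing expressly applies it to harm.

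*Benefit and harm are not read from different populations.* A reader might infer this as well. But the instrumental variable analysis complements intention to treat, and both main chi-squared comparisons use the same groups. This objection stands in full.

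*The dilution is small as planned.* At 90% acceptance, 10 points become 9. The larger losses in the table need two or more times the refusal expected, and the plan treats substantial refusal as a contingency. This stands and limits the weight of the point.

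*A safety population may be defined in an analysis plan not shown.* That is possible, and an omission alone would be no finding. But the article does not leave the matter open: it states the rule, the groups and the test. Adding a table by treatment received would not conflict with that rule.

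*Refusers select themselves.* Regrouping by treatment received breaks the randomised comparison, and in a pragmatic comparison of strategies, harm by offer is a legitimate quantity. This stands as a reason to keep the intention-to-treat comparison and not replace it.

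**Conclusion.** The point holds as a cheap improvement. As written, grade 3–4 toxicity is compared by offer of SBRT, with refusers on standard radiotherapy counted in the SBRT arm. This reduces the observed excess by the refusal proportion: 10% in relative terms at the planned acceptance, and 30% to 50% if acceptance were 70% to 50%. The relative loss rests on two assumptions: negligible movement from control to SBRT, which the protocol itself expects, and refusers whose underlying risk resembles that of accepters. The figures in points and power rest also on assumed harm rates, because the document gives none.

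It would go too far to say that refusal always makes SBRT look safer on fractures. The MRI scheduled in the SBRT arm only works in the opposite direction, and the net effect is unknown.

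**What to change.** Keep the intention-to-treat comparison. Beside it, pre-specify a table of grade 3–4 toxicity and vertebral compression fractures by radiotherapy actually received (SBRT or standard). State that the instrumental variable analysis, if triggered, also covers toxicity.

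The cost is one extra table from data already collected, with no additional patients or visits. Its groups are not purely randomised, so it should be labelled as such and read with the intention-to-treat comparison. It does not remove the MRI detection difference for fractures, which should be noted beside those rows.

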### Patient recruitment

At enrollment, patients give informed consent for collection of clinical and survival data, and can opt-in to provide PROMs. In addition, in a separate question, we ask patients for their broad consent for future randomization in trials that will investigate the effectiveness of experimental treatments [14]. Patients within the PRESENT cohort who meet the VERTICAL inclusion criteria (Table 1) are identified as a sub cohort of eligible patients. Eligible patients are PROMs-providing participants of the PRESENT cohort, have untreated symptomatic spinal metastases, and have given consent for broad randomization to experimental interventions. Patients are excluded if they are not able to undergo SBRT, have severe or progressive neurological deficits, received previous radiotherapy or surgery to the index site(s), or have a life expectancy less than three months. After a protocol amendment on September 23, 2015 to adjust to developments in clinical practice, also patients with non-spinal bony metastases are eligible.

**Table 1 Tab1:** Selection criteria for the VERTICAL study

Inclusion criteria	Exclusion criteria
Participant in PRESENT cohort	Lesion in C1, and C2
Filling out PRESENT-questionnaires	Contraindication for MRI if MRI is indicated
Broad consent for randomization to experimental interventions	Radiosensitive histology such as multiple myeloma
Histologic proof of malignancy	Unable to undergo SBRT treatment
Imaging evidence of bone metastases	Patient with < 3 months life expectancy
For spinal lesions, per lesion no more than 3 consecutive spine segments involved with one unaffected vertebral body above and below	Chemotherapy or systemic radionuclide delivery within 24 h before and after SBRT
No more than 2 painful lesions needing treatment	Previous EBRT or SBRT to same level
For spinal lesions, no compression of spinal cord	For spinal lesions, unstable spine requiring surgical stabilization
No or mild neurological signs^a^	Severe, worsening or progressive neurological deficit
KPS > 50 and pain score > 3^b^	

*VERTICAL* randomized controlled trial comparing conVEntional RadioTherapy with stereotactIC body radiotherapy in patients with spinAL metastases; *PRESENT* Prospective Evaluation of interventional StudiEs on boNe meTastases (PRESENT) cohort; *MRI* magnetic resonance imaging; *SBRT* stereotactic body radiotherapy; *EBRT* external beam radiotherapy; *KPS* Karnofsky performance score

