**Fig. 1 Fig1:**
[figure not shown]
Study design VERTICAL study A large observational cohort of patients with bone metastases is recruited and their outcomes regularly measured (*dark blue* box). Patients within the PRESENT cohort who meet the VERTICAL inclusion criteria are identified as a sub cohort of eligible patients (*light blue* box). Randomly selected patients (*orange* box) are offered the SBRT intervention. The outcomes of these randomly selected patients (i.e. the intervention arm) are then compared with the outcomes of eligible patients not randomly selected who receive standard of care (i.e. the control arm, *brown* boxes)

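### Intention to treat is stated, but the control arm is worded as non-selected patients who were irradiated, a post-selection condition that the intervention arm does not carry

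*Protocol article*

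**What the plan says.** The Data analysis section opens with the principle: "Data will be analyzed according to the intention to treat principle". The next sentence names the groups. "Data of eligible patients who were randomly offered stereotactic radiotherapy" "will be compared with eligible patients who were not randomly selected and received standard radiotherapy".

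The Random selection section gives the same comparison: "Outcomes in randomly selected patients are compared with the outcomes in eligible patients not randomly selected who received standard radiotherapy". It also says how the offer follows selection: "The radiation oncologist will offer the experimental intervention (i.e. SBRT) to the randomly selected patients". Those who decline get standard radiotherapy. They remain in the intervention arm, because the Data analysis section plans an instrumental variable analysis in case refusal is substantial.

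The Fig. 1 legend equates the randomly selected patients with the intervention arm. It describes controls more broadly, as non-selected patients on standard of care. Under the dropout rule in Data analysis, patients who do not survive three months, or cannot supply pain scores and analgesic use, count as non-responders.

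**The concern.** Whether a patient is irradiated becomes known only after random selection. If it is a condition for entering the control arm, that arm is defined partly by treatment received. The intervention arm is defined by selection alone, so the two arms pass through different filters.

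Consider two patients with the same course, each deteriorating or dying before any radiotherapy. The selected patient is analysed and counts as a non-responder. The non-selected patient does not meet the wording of the control group and drops out of the denominator. The comparison is then no longer between groups formed by chance, and an analyst could exclude such controls while following the sentence to the letter. The planned instrumental variable analysis is exposed too, because using selection as the instrument requires arms defined by selection only.

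**Working it through.** **Inputs from Sample size considerations:** response 60% after standard radiotherapy and 85% after SBRT; 90% acceptance of the offer; one-sided α 5%; power 80%; 49 per arm, 55 with 10% dropout. **Assumed, not in the documents:** a share q of each arm is never irradiated.

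**1. Reproduce the planned size.**
- Response in the selected arm with refusers kept: 0.9 × 0.85 + 0.1 × 0.60 = 0.825.
- Two proportions, pooled variance, no continuity correction: n = [z₀.₉₅√(2p̄(1−p̄)) + z₀.₈₀√(p₁(1−p₁) + p₂(1−p₂))]² / (p₂−p₁)².
- With p₁ = 0.60, p₂ = 0.825, p̄ = 0.7125: n = [1.645 × 0.640 + 0.842 × 0.620]² / 0.225² ≈ 49 per arm.
- Dropout: 49 / 0.9 = 54.4, so 55.

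The stated figures are reproduced with an intervention arm that includes refusers. This supports reading that arm as analysed by selection, but does not prove it: a two-sided test of 60% against 85% also gives 49, though it contradicts the stated one-sided α. (The 15% difference printed beside these figures fits neither pair of rates; that is a separate matter.)

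**2. Shift if only controls are filtered.** Take 60% and 82.5% as the rates among irradiated patients, and count the never-irradiated as non-responders.
- By selection status: 0.825(1−q) − 0.60(1−q) = 0.225(1−q).
- Literal wording: 0.825(1−q) − 0.60.
- Shift, literal minus by selection: −0.60q.

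| q | By selection (points) | Literal (points) | Shift (points) |
|---|---|---|---|
| 2% | 22.05 | 20.85 | −1.2 |
| 5% | 21.4 | 18.4 | −3.0 |
| 10% | 20.25 | 14.25 | −6.0 |

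**3. Effect on the test.** Normal approximation, one-sided 5%, 55 selected per arm. Under the literal wording the control arm shrinks to about 55(1−q), that is 54, 52 and 50. Type I error is computed with 60% response among irradiated patients in both arms.

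| q | Power, by selection | Power, literal | One-sided type I error, literal |
|---|---|---|---|
| 2% | 0.82 | 0.78 | 0.038 |
| 5% | 0.78 | 0.66 | 0.025 |
| 10% | 0.72 | 0.46 | 0.012 |

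**4. Direction.** If the excluded controls respond at rate r, the control rate by selection is 0.60(1−q) + rq, and the shift becomes q(r − 0.60). It is negative for r below 60% and positive above it. At q = 5% it runs from −3.0 points (r = 0) to +2.0 points (r = 100%).

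**The case against.** The strongest reply is that the phrase describes what controls get and does not filter them. The abstract says plainly that the non-selected patients receive standard radiotherapy, and the Fig. 1 legend and the Discussion speak of standard of care in the same way. The intention-to-treat statement stands directly before the sentence, and the dropout rule directly after it makes no distinction by arm. The cohort consists of patients referred for treatment, and short life expectancy and a spine needing surgical stabilisation are exclusions, so q may be small. Under the assumption used above, the bias also works against SBRT: it costs power and does not create a false claim of benefit.

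Much of this stands, and it limits the severity. It does not remove the point. The two sentences at issue are the ones that say whose outcomes are compared. The dropout rule acts on patients already in the comparison, and a never-irradiated control who still reports pain scores is not a dropout under it. Nothing in the text says that such a control stays in. The Discussion itself calls the population fragile, so q need not be zero.

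Two stronger readings are tempting but not supported:

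- A reader might infer that the intervention arm is conditioned as well, on the offer having been made. The Random selection section and the Fig. 1 legend define that arm by selection, the offer goes to the selected patients without a further stated filter, and refusers are kept. *Offered* in Data analysis is loose wording for *selected*.
- A reader might infer that the Table 1 exclusion "Chemotherapy or systemic radionuclide delivery within 24 h before and after SBRT" removes patients after selection, and only in the SBRT arm. Table 1 defines the sub cohort from which patients are then selected. The criterion can be read as a scheduling condition judged at that stage, and nothing in the text applies it afterwards.

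**Conclusion.** The concern holds for the control arm only. As worded in both places, controls are conditioned on treatment received after random selection, which conflicts with the stated intention to treat and has no counterpart in the intervention arm. The shift is −0.60q: about 1 point at q = 2% and 6 points at q = 10%. That rests on an assumed q, on equal q in both arms, and on non-response among those never irradiated. Neither the size nor the sign can be fixed from the documents. Since the phrase may be purely descriptive, this is a clarification worth making before analysis, not a demonstrated flaw that invalidates the design.

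**What to change.** Reword the comparison in Random selection and in Data analysis to this effect: the primary comparison includes all patients eligible at the time of random selection, analysed by selection status (selected for the SBRT offer, or not selected), regardless of what was offered or received; the non-responder rule for dropouts applies to both arms alike. In Data analysis, replace *offered* with *selected* so that the two sections agree. Account for treatment actually received only in the planned instrumental variable analysis.

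The cost is two sentences. The sample size is unaffected, because 49 per arm already follows from the refusal-diluted rates. Patients in the sub cohort are questionnaire-completing participants of PRESENT who consented to data collection, so no new data collection is needed.

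### The sample size is inflated as if dropouts leave the analysis, but they are kept as non-responders; planned power is then about 70–72%, not 80%

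*Protocol article*

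**What the plan says.** All references are to the protocol article.

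Under Sample size considerations, the control assumption is that "we expect a pain response in 60% of patients following standard radiotherapy", and the rate after stereotactic treatment is put at 85%. On uptake: "We expect that approximately 90% of patients who are offered SBRT treatment, will accept the offer". The calculation reads "Taking a one-sided α of 5% and a power of 80%, we require 49 patients per treatment arm", followed by the allowance for loss: "to allow for a 10% drop out rate, recruitment of 55 patients per group is intended".

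Under Random selection, patients who decline the offer receive standard radiotherapy.

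Under Data analysis, the comparison is by intention to treat, with a χ2 test of the two response proportions. Dropout means death before three months or inability to supply pain scores and analgesic use. For these patients "a worst-case analysis will be performed: dropped-out patients will be classified as non-responders". No other rule for dropouts is given.

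**The concern.** The two sections treat the same patients differently. Dividing by 0.9 is the standard allowance for patients who will not be in the analysis: recruit 55, lose about 10%, and compare about 49 per arm at the assumed rates. The analysis rule loses nobody. All 55 stay in the denominator, and the expected 10% count as failures in both arms. This multiplies both response rates, and therefore the difference between them, by 0.9, and the sample size makes no allowance for it.

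At stake is the power figure on which the trial's size is justified. If the plan's own dropout expectation is met exactly, the chance of missing the assumed effect is larger than the stated 20%.

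**Working it through.** **Inputs.** Control 60%, stereotactic 85%, acceptance 90%, one-sided α 5%, power 80%, dropout 10%, 55 per arm (Sample size considerations); 1:1 selection, refusers given standard radiotherapy (Random selection); dropouts scored as non-responders (Data analysis). Refusers are taken to respond at the control rate.

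**Step 1: the plan's 49.**
- Offered arm by intention to treat: 0.9 × 0.85 + 0.1 × 0.60 = 0.825.
- n = [z(0.95)·√(2p̄q̄) + z(0.80)·√(p₁q₁ + p₂q₂)]² / (p₂ − p₁)², with p̄ the mean of the two rates and q = 1 − p.
- p̄ = 0.7125, so 2p̄q̄ = 0.4097; p₁q₁ + p₂q₂ = 0.2400 + 0.1444 = 0.3844.
- n = (1.645 × 0.6401 + 0.842 × 0.6200)² / 0.225² = 1.5746² / 0.050625 = 48.98, so 49. This matches the article.
- 49/0.9 = 54.4, so 55. This also matches.
- Power with 49 assessable patients per arm is 80.0%.

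**Step 2: apply the dropout rule.**
- Control: 0.9 × 0.60 = 0.54. Offered arm: 0.9 × 0.825 = 0.7425. Difference 0.2025.
- p̄ = 0.64125, 2p̄q̄ = 0.4601; p₁q₁ + p₂q₂ = 0.2484 + 0.1912 = 0.4396.
- Power = Φ{[0.2025 − 1.645·√(0.4601/55)] / √(0.4396/55)} = Φ{(0.2025 − 0.1504)/0.0894} = Φ(0.582) = 72.0%.
- Exact binomial enumeration of the same uncorrected one-sided test gives 71.9%.

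**Step 3: why 55 is not enough.** Shrinking the difference by 0.9 alone raises the required n by 1/0.81. Both rates also move towards 50%, which raises the variance. For 80% power: n = (1.645 × 0.6783 + 0.842 × 0.6630)² / 0.2025² = 1.6737² / 0.04101 = 68.3, so 69 per arm. This shows the size of the gap; it is not a proposal to recruit more.

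**Step 4: other readings of the 49.**

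| Reading | n per arm for 80% | Power at 55 under the rule |
|---|---|---|
| 60% v 82.5%, one-sided | 49 | 72.0% |
| 60% v 85%, two-sided | 49 | 70.3% (54% v 76.5%) |
| 60% v 85%, one-sided | 39 | 80.4% |
| 60% v 75%, one-sided | 120 | 42.2% (54% v 67.5%) |

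Only the first two reproduce 49. The last row takes the article's words "to show a statistically significant difference of 15% in pain response" literally. That figure matches neither 85 − 60 = 25 nor 82.5 − 60 = 22.5; it is a separate inconsistency and does not affect this result.

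**The case against.** Several objections deserve an answer.

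*The assumed rates may already count dropouts as failures.* The article speaks of patients who undergo radiotherapy, and the denominators in the cited sources cannot be seen here. If so, power at 55 per arm would be 84.0%. But the 10% allowance would then be unnecessary, so the plan's own step implies rates among assessable patients. The assumption should be stated; it does not remove the mismatch.

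*The rule may be only a sensitivity analysis.* The term worst-case allows that reading. Yet the sentence follows directly on the intention-to-treat statement, says what happens when patients drop out, and is the only dropout rule given.

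*One reading keeps 80%.* Ignoring refusals at one-sided 5% gives 80.4%, but it needs only 39 per arm and disregards the stated 90% acceptance.

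*The shortfall is modest and creates no bias.* This stands. With equal dropout the rule pulls the observed difference towards zero, so it is conservative for superiority and does not raise the false-positive rate.

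A reader might go further and infer that missing questionnaires will be commoner in controls, so that the rule manufactures a benefit for stereotactic treatment. The article does not support that. Both arms complete the same PRESENT questionnaires on one schedule, and filling them out is an inclusion criterion for everyone. The extra MRI in the stereotactic arm is at six months, after the endpoint, unless a fracture is suspected sooner. The Discussion expects few control patients to withdraw. Unequal rates that inflate the type I error can be chosen, but none come from the document, and the opposite imbalance would bias against stereotactic treatment.

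**Conclusion.** The stated 80% power is wrong as written, because the sample size step and the analysis rule make incompatible assumptions about dropouts. On the plan's own inputs, power with 55 per arm is about 72% at one-sided 5%, so the type II error is about 28% instead of 20%. Under the two-sided reading of 60% versus 85%, power is about 70%. The result assumes that the response rates are among assessable patients, that refusers respond at the control rate, and that dropout is 10% in each arm and unrelated to acceptance.

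The finding does not show that the primary rule is invalid, that multiple imputation should replace it, or that the trial must be enlarged. Replacing the rule for living patients would also make the 72% inapplicable. The article gives no split between deaths and missing data from which a new figure could be computed.

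The label worst-case is loose. The rule is the worst outcome for each patient, but applied equally to both arms it is not the worst case for a superiority claim. With missing controls counted as responders, the expected rates would be 0.54 + 0.10 = 64% versus 74.25%, a gap of 10.25 points instead of 20.25.

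**What to change.** Keep 55 per arm and keep the non-responder rule. In Sample size considerations, replace the 80% claim for the recruited sample with a statement that 49 assessable patients per arm would give 80%, whereas 55 per arm with 10% dropout scored as non-response gives about 72% (54% versus 74.25%, one-sided 5%). If the 49 was in fact derived from 60% versus 85% two-sided, the figure to state is about 70%. Say that the 60% and 85% are rates among assessable patients and that dropout is taken as equal in the arms.

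Optionally, call the rule non-responder imputation and add one sensitivity analysis in which missing patients in the stereotactic arm count as non-responders and missing controls as responders.

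The cost is a less favourable stated power and, if the option is taken, one extra analysis. No additional patients or data are needed.
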